# Weight loss before total joint arthroplasty using a remote dietitian and mobile app: study protocol for a multicenter randomized, controlled trial

**DOI:** 10.1186/s13018-020-02059-w

**Published:** 2020-11-13

**Keywords:** Obesity, Obesity, Morbid, Weight loss, Knee osteoarthritis, Osteoarthritis, Hip, Mobile applications, Smartphone, Telemedicine, Nutritionists, Arthroplasty, Dietitian, Preoperative Period, Randomized Controlled Trial, Multicenter Study

## Abstract

**Background:**

The months prior to elective surgery may present an opportunity for patients to initiate behavior changes that will simultaneously ready them for surgery and improve their overall health status. An upcoming elective total joint arthroplasty (TJA) may serve as motivation for patients with severe obesity (body mass index [BMI]> 40 kg/m^2^) to lose weight, as it may optimize clinical outcomes following TJA and help them become eligible for TJA since some surgeons use a BMI of 40 kg/m^2^ as a cut-off for offering surgery in an effort to optimize outcomes.

**Methods:**

The purpose of this multicenter randomized, controlled trial is to assess the feasibility and efficacy of a 12-week remote dietitian (RD) supervised dietary and physical activity weight loss intervention and mobile app for 60 patients with severe obesity prior to undergoing TJA. Intervention participants will receive access to a smartphone app and connect with an RD who will contact these participants weekly or bi-weekly via video calls for up to nine video calls. Together, participants and RDs will set goals for lifestyle modifications, and RDs will check on progress towards achieving these goals using in-app tools such as food logs and text messages between video calls. All patients will be encouraged to lose at least 20 pounds with a goal BMI < 40 kg/m^2^ after 12 weeks. Individuals randomized to the control group will receive clinical standard of care, such as nutritionist and/or physical therapy referrals. Outcome and demographic data will be collected from blood serology, chart review, mobile app user data, pre- and postintervention surveys, and phone interviews. The primary outcome measure will be weight change from baseline. Secondary outcome measures will include percentage of patients eligible to undergo TJA, number of sessions completed with dietitians, self-reported global health status (PROMIS Global Health scale), self-reported joint-specific pain and function (Knee injury and Osteoarthritis Outcome Score (KOOS) or Hip disability and Osteoarthritis Outcome Score (HOOS)), and serologies such as hemoglobin A1c, total lymphocyte count, albumin, and transferrin. Qualitative responses transcribed from phone interviews about the intervention will also be analyzed.

**Discussion:**

This will be the first study to assess pre-operative weight loss in patients with severe obesity anticipating orthopaedic surgery using an RD and mobile app intervention aimed at helping patients become eligible for TJA.

**Trial registration:**

Registered on 1 April 2020 at Clincialtrials.gov. Trial number is NCT04330391.

## Background

Surgery is a major decision for many patients and often involves reflection on personal health behaviors when weighing the risks and benefits of procedures [1, 2]. Positive preoperative lifestyle factors including nonsmoking status, increased physical activity, and normal body mass index (BMI) are associated with improved postoperative outcomes [3–5]. However, time pressure, fiscal constraints, and limited provider experience encouraging lifestyle changes may hamper effective counseling during the preoperative period [6, 7]. Digital technologies have recently been proposed as a potential solution to the barriers of preoperative lifestyle counseling [2].

A previous remote dietitian (RD) intervention for overweight pregnant women in 2018 demonstrated high satisfaction with dietitians and a desire for an integrated mobile app before a motivating event like childbirth [8]. An upcoming elective surgery may be similarly motivating for patients to make lifestyle modifications, especially for patients with severe obesity who may become eligible for surgery if they reduce their BMI below the 40 kg/m^2^ maximum for total joint arthroplasty (TJA) used by some surgeons as a cutoff for offering surgery in an effort to optimize outcomes [9].

A recent retrospective review of patients with severe obesity (BMI > 40 kg/m^2^) who lost weight before total knee arthroplasty (TKA) found that losing at least 20 pounds before surgery was associated with fewer discharges to a facility and shorter lengths of stay, but losing just five or 10 pounds had no effect [10]. A 2018 study of physical activity after TKA found a combined dietitian and financial incentive intervention increased step counts and physical activity following TKA [11].

However, despite multiple investigations regarding the association between lifestyle interventions and postoperative outcome, there is a dearth of research regarding success of weight loss interventions specifically prior to TJA. Although there are three studies of pre-operative dietary interventions prior to TJA, only one study concluded before surgery and this study did not compare pre-operative weight loss to a control group [12–14]. A 2015 review of nonsurgical, non-pharmacologic weight loss interventions in patients with obesity prior to TJA found that there was limited research on the association between weight loss prior to TJA and pre- and post-operative outcomes, and that future studies should address the safety, optimal timing, duration, amount of targeted weight loss, and delivery of pre-TJA interventions [15]. In addition, a recent study of patients about to undergo TKA or who were recently post-TKA found that patients wanted a weight loss program that started before surgery, was at least 6 months in duration, and focused on both diet and exercise [16].

In our proposed mixed-methods, multicenter randomized controlled trial (RCT), our primary aim is to assess the feasibility and efficacy of a 12-week RD supervised dietary and physical activity weight loss intervention and mobile app for patients with severe obesity prior to undergoing TJA. We hypothesize that a 12-week RD supervised dietary and physical activity weight loss intervention and mobile app for patients with severe obesity who are TJA candidates will result in (1) greater weight loss than clinical standard of care, (2) a higher percentage of patients eligible to undergo TJA by having a BMI below the standard cutoff of 40 kg/m^2^ within 3 months of enrollment, and (3) a higher percentage of patients undergoing TJA within 6 months of enrollment.

## Methods/design

### Study design

This mixed-methods study is a prospective, two-arm, randomized controlled trial that will take place remotely and involve patients at two institutions. The trial includes a 12-week intervention period followed by a 3-month follow-up period for selected secondary outcomes. Various outcomes will be assessed at baseline, 6 weeks, 12 weeks, and 24 weeks (Fig. 1).

**Fig. 1 Fig1:**
[figure not shown]
Flow diagram. Randomized controlled trial design

### Eligibility criteria

#### Inclusion criteria

Subjects must be greater or equal to 18 years of age.Subjects must have 40 kg/m^2^ < BMI < 47 kg/m^2^ recorded in the electronic medical record within 6 months prior to enrollment. Weights recorded earlier than 2 weeks before enrollment must be verified by an additional weight measurement using study scales sent to subjects’ homes or in clinic during enrollment.Subjects must have end-stage knee or hip osteoarthritis, avascular necrosis, or rheumatoid arthritis with recommended primary, unilateral TJA by orthopaedic surgeons at two institutions.Subjects would consider undergoing TJA if eligible.Subjects own a smartphone, tablet, or personal computer compatible with video calls and a specified mobile app. The device must have a camera, access to Internet, and Apple App Store or Google Play.All subjects must be willing to comply with the requirements of the study and provide informed consent prior to enrollment. Evidence of a signed and dated informed consent document indicating that the subject (or a legally acceptable representative) has been informed of all pertinent aspects of the study must be obtained prior to data collection.

#### Exclusion criteria

Subject’s enrollment BMI is less than 40 kg/m^2^ or greater than 47 kg/m^2^ when verified by study scale at subjects’ homes or by weight recorded at enrollment in clinic. BMI over 47 kg/m^2^ would require inappropriate weight loss of over three pounds per week to reach a BMI of 40 kg/m^2^ after 12 weeks.Subjects unable to comprehend and speak English.Subjects undergoing revision TJA.Subjects undergoing bilateral TJA.Subjects planning to undergo bariatric weight loss surgery in the next 6 months.Subjects planning to be pregnant in the next 6 months.Subjects unwilling or unable to use a smartphone, tablet, or personal computer with home Internet access.Subjects are incarcerated.Subjects are pregnant women or vulnerable individuals.

### Patient population and recruitment procedure

Patients of fellowship trained arthroplasty surgeons at two institutions will be identified as potentially eligible for the study based on 40 kg/m^2^ < BMI < 47 kg/m^2^ recorded in the patient’s medical record within the last 6 months and recommended primary, unilateral total knee or hip arthroplasty. For patients identified as potentially eligible while in clinic, an orthopaedic surgeon will introduce the patient to the study, and a member of the research team (research assistant or trainee) will conduct an eligibility screening and obtain verbal consent either in-person or by phone. For patients identified as potentially eligible outside of clinic, a member of the research team will call the patient to introduce the study, and conduct eligibility screening and consent on the phone.

Eligible, interested, and consented patients will be provisionally enrolled, and all subjects will be shipped a standard bathroom scale to their home (Fig. 1). This initial enrollment is provisional, as subjects will be required to verify enrollment BMI by (a) submitting a photo to the study team of their study scale during a weigh-in that displays their body weight, or by (b) recording a baseline weight at an onsite healthcare facility within 2 weeks of provisional enrollment. Once enrollment BMI is verified to be 40 to 47 kg/m^2^, subjects will be fully enrolled and randomized to the intervention arm or clinical standard of care arm via REDCap. Subjects will be given a $40 check for enrolling, which includes (1) taking a baseline survey, (2) recording the baseline weight at an onsite healthcare facility or with a home study scale, and (3) getting baseline labs within 2 weeks of the baseline weight. Baseline weights will be recorded without shoes or outer clothing (e.g., coats). All subjects will be given a $20 check if they can verify a mid-study weight during week 6 of the study by recording a weight at any onsite healthcare facility or by submitting home study scale photos. All subjects will receive a $40 check for completing an end-of-study survey, weight, and labs at 10–14 weeks after enrollment.

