### Randomization and allocation

Enrolled subjects will be randomized into two groups with an allocation ratio of 1:1 in blocks of four. The allocation table will be randomly generated via Microsoft Excel by an independent third-party clinical researcher, uploaded to the study REDCap randomization model, and will not be accessible to study staff within REDCap. Group assignment will be revealed via the REDCap model only at the time of randomization during enrollment following informed consent procedures and enrollment BMI verification.

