### Arms

Intervention participants will download a telemedicine online/smartphone app (Nutrimedy, Brookline, MA, USA) and be connected at enrollment with a certified registered dietitian who will contact intervention participants weekly or bi-weekly via video calls and unlimited in-app text messaging for up to 3 months. The first week will include either one 55-min video session or two 25-min sessions. Weeks 2–4 will have weekly 25-min video calls, and weeks 5–12 will have biweekly 25-min sessions for a total of 8–9 sessions over 12 weeks. Together, participants and dietitians will come up with goals for the 12 weeks, and dietitians will check on progress toward these goals using in-app tools such as food logs and messaging between video calls. All patients will be encouraged to lose at least 20 pounds with a goal BMI < 40 kg/m^2^ after 12 weeks.

Dietitians will use principles of motivational interviewing, cognitive behavioral interventions, and the socioecological model to remotely provide behavior and lifestyle interventions. Motivational interviewing is a patient-centered, collaborative approach to counseling in which the dietitian elicits personally relevant reasons from subjects to make behavior changes that may promote weight loss. Dietitians and patients then structures goals for lifestyle modifications around these personal motivations [17]. Cognitive behavioral interventions provide subjects with strategies to change cognitive processes to alter behaviors, such as self-monitoring (e.g., recording food intake, weight, and exercise), stimulus control (e.g., keeping less healthy foods in cabinets out of sight), and accountability by having frequent check-ins with dietitians [18]. The socioecological model proposes that multiple levels of influence including intrapersonal (e.g., knowledge and attitudes), interpersonal (e.g., family and friends), and community factors (e.g., organizations, workplaces, neighborhoods) can impact energy-balance behaviors and weight outcomes [19]. Dietitians will promote the adoption and maintenance of behaviors across multiple levels of influence.

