### Surveys

All participants will complete a baseline survey at enrollment, and an end-of-study survey 10–14 weeks after enrollment (Additional files 1, 2 and 3). Questions about weight loss methods and the level of interest and confidence in weight loss were taken from Cleveland et al. [20]. Questions about motivation for weight loss were adapted from Meyer et al. [21]. Questions about exercise, diet, and goal setting routines were taken from the Paving Wheel Wellness score by Frates [22]. Items querying food frequency, hours spent doing physical activity, demographics, and opinions about the intervention were adopted from Seward et al. [8]. Alcohol and tobacco use questions were taken from the AUDIT-C alcohol screen and World Health Organization Global Tobacco Surveillance System [23, 24]. Surveys also included the Lower Extremity Activity Scale (LEAS) [25], PROMIS-Global Health scale, and the Knee injury and Osteoarthritis Outcome Score (KOOS) or Hip disability and Osteoarthritis Outcome Score (HOOS) depending on the joint [26, 27]. In addition to the demographic information collected on baseline surveys, we will also review each subject’s electronic medical record to obtain medication lists.

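### Randomisation waits only for consent and a verified BMI, so baseline labs, and possibly the baseline survey, can be collected after allocation; only secondary change scores are exposed

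*Protocol article*

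**What the plan says.** All references are to the Protocol article.

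- **What triggers randomisation.** Patient population and recruitment procedure: "Once enrollment BMI is verified to be 40 to 47 kg/m^2^, subjects will be fully enrolled and randomized". Randomization and allocation says that the assignment is shown "only at the time of randomization during enrollment following informed consent procedures and enrollment BMI verification". Neither sentence names the labs or the survey.
- **When the labs are due.** Patient population and recruitment procedure counts "getting baseline labs within 2 weeks of the baseline weight" among the tasks covered by the enrolment payment. The anchor is the weight, not the randomisation.
- **When the survey is due.** Surveys: "All participants will complete a baseline survey at enrollment". Its order relative to allocation is not given.
- **When the intervention starts.** Arms: intervention participants will "be connected at enrollment with a certified registered dietitian who will contact intervention participants weekly or bi-weekly". On the opening sessions: "The first week will include either one 55-min video session or two 25-min sessions".
- **Who knows the arm.** Blinding: participants are not blinded.
- **How the data are used.** Labs records the serologies at baseline and at the end of the study. Statistical analyses compares the arms by t tests on differences over time in continuous variables. For the agree/disagree survey items it compares the follow-up answers only.

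**The concern.** A baseline is safe for a between-arm comparison of change when it is fixed before the participant knows the arm and before treatment can act. Here the event that opens randomisation, the verified weight, also anchors the window for the blood draw. A participant can therefore be weighed, randomised and counselled, and then have blood drawn inside the permitted window.

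This order is plausible in a remote trial. The weight can be verified by a photograph from home, whereas the labs need a blood draw, and the Discussion itself doubts that both sets of labs can always be collected.

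Two things are at stake:

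- **Labs.** Any early effect of counselling enters the baseline of the intervention arm and is subtracted from the measured change, so the between-arm difference shrinks.
- **Patient-reported scores.** A participant who already knows the assignment may answer the PROMIS or KOOS/HOOS items differently, whether pleased or disappointed. This can happen in both arms, and the bias in the change score can go either way.

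**Working it through.** **1. Order of steps**

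| Step | What the text fixes | Must it precede allocation? |
|---|---|---|
| Consent | before allocation | yes |
| Verified BMI (baseline weight) | before allocation | yes |
| Baseline labs | within 2 weeks of the weight | not stated |
| Baseline survey | at enrolment | not stated |
| Link to dietitian | at enrolment, intervention arm | follows allocation |

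Enrolment covers both a provisional and a full step, and the full step coincides with randomisation. A survey taken at enrolment can thus fall on either side of allocation.

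**2. Sessions that can precede the draw**

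The plan's own total comes first (Arms). Week 1 has 1 or 2 sessions, weeks 2–4 have 3, and weeks 5–12, at one every two weeks, have 4.

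- 1 + 3 + 4 = 8 and 2 + 3 + 4 = 9, which reproduces the stated 8–9.
- By the end of week 2: 1 + 1 = 2 of 8 = 25%, or 2 + 1 = 3 of 9 = 33%.

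This assumes no delay from weight to randomisation or from randomisation to first session, and a draw on day 14.

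**3. Share of a lab effect absorbed into the baseline**

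Let the full effect at the end-of-study draw be δ, reached at week T, and assume that it builds up linearly from enrolment. The documents give no time course, so this is an assumption. A baseline drawn L weeks after the start already contains δ × L/T. The between-arm difference in mean change becomes δ − δ × L/T = δ × (1 − L/T).

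With L = 2 and the stated end-of-study window of 10–14 weeks:

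| T (weeks) | Interval left, T − 2 | Share absorbed, 2/T |
|---|---|---|
| 10 | 8 | 20% |
| 12 | 10 | 17% |
| 14 | 12 | 14% |

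These figures apply if every intervention participant has the 2-week lag. Otherwise L is the mean lag: a mean of 1 week with T = 12 gives 1/12 = 8%, and draws before the first session give 0. An effect that appears early would lose more than the linear figure.

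**4. Which outcomes are exposed**

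- Weight (primary), BMI and the outcomes derived from them: not exposed, because the verified weight precedes randomisation.
- Lab changes: exposed if analysed as change.
- PROMIS and KOOS/HOOS: exposed if analysed as change from a survey answered after allocation. No size can be derived from the documents.
- Agree/disagree items: the test uses follow-up answers only, so a late baseline does not enter it. It bears only on the stated assumption that baseline answers are similar.

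Statistical analyses names weight measures as its examples of differences over time. I take labs and patient-reported scores to be handled the same way.

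The sample size rests on weight and does not change.

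**The case against.** The strongest case on the other side is that the text can be read as placing everything before allocation. The payment sentence, "Subjects will be given a $40 check for enrolling, which includes (1) taking a baseline survey", goes on to the weight and the labs, so enrolling appears to contain all three, and it is enrolled subjects who are randomised. The lab window can also mean before the weight. The order of steps within a visit is something a condensed article may leave to the full protocol, and the flow diagram is not shown.

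Part of this stands. The survey order is ambiguous rather than wrong, and nothing requires a late draw. It does not settle the labs, however. The payment sentence sets a condition for a check, whereas the two sentences that govern randomisation name consent and BMI only. The window is open on both sides of the weight.

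A reader might infer more than the documents support:

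- *That randomisation follows the weight immediately.* No interval is given, so the figures above are a zero-delay worst case, not an expected loss.
- *That the primary result is biased.* It is not, given the order of weight and randomisation.
- *That only the intervention arm is affected.* This is true of early treatment effects on labs. It is not true of survey answers, since controls also know their arm.
- *That all survey comparisons are affected.* The agree/disagree items are compared at follow-up only.

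**Conclusion.** The point holds in a limited form. As written, the plan allows a baseline lab draw after allocation and after the first dietitian sessions, and it does not exclude a baseline survey answered with the arm known. The exposure is confined to secondary lab changes and to patient-reported scores analysed as change.

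For labs, the worst case is 25–33% of sessions held before the draw and 14–20% of the effect absorbed. This rests on no delay at any step, a day-14 draw for all intervention participants and a linear build-up. Realistic lags would give less under the same build-up. For patient-reported scores, neither direction nor size can be stated. This is a cheap improvement to secondary outcomes, not a threat to the trial's main conclusion.

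**What to change.** 1. **Survey.** Set REDCap so that the randomisation step opens only once the baseline survey is complete.
2. **Labs.** Ask for the baseline draw before allocation is revealed where feasible. Randomisation need not wait for it.
3. **Definition of a lab baseline.** In both arms alike, count a value as baseline only if it was drawn on or before the randomisation date. Otherwise treat the baseline as missing and compare end-of-study values between arms. Report the number of late draws by arm.

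The cut-off should not be the first dietitian session. Controls have none, so that rule would discard baselines in the intervention arm only. Holding back the first session until the draw is done is also unattractive, because the primary endpoint is timed from enrolment and treatment time before it would shrink.

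The cost is one REDCap rule and a sentence or two in the protocol. Some participants will lack a valid lab baseline, or randomisation may wait briefly for the survey. The sample size is unchanged.
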